## Abstract

Most of the patients with head and neck squamous cell carcinoma (HNSCC) are diagnosed with locally advanced disease. Standards of care for curative-intent treatment of this patient group are either surgery and adjuvant radio(chemo)therapy (aRCT) or definitive chemoradiation. Despite these treatments, especially pathologically intermediate and high-risk HNSCC often recur. The ADRISK trial investigates in locally advanced HNSCC and intermediate and high risk after up-front surgery if the addition of pembrolizumab to aRCT with cisplatin improves event-free sur-vival compared to aRCT alone. ADRISK is a prospective, randomized controlled investiga-tor-initiated (IIT)-phase II multicenter trial within the German Interdisciplinary Study Group of German Cancer Society (IAG-KHT). Patients with primary resectable stage III and IV HNSCC of the oral cavity, oropharynx, hypopharynx and larynx with pathologic high (R1, extracapsular nodal extension) or intermediate risk (R0 <5 mm; N≥2) after surgery will be eligible. Two hun-dred forty patients will be randomly assigned (1:1) to either standard aRCT with cisplatin (standard arm) or aRCT with cisplatin + pembrolizumab (200 mg iv, in 3-week cycle, max. 12 months) (interventional arm). Endpoints are event-free and overall survival. Recruitment started in August 2018 and is ongoing.

## Introduction

Up to 60% of patients diagnosed with head and neck squamous cell carcinoma (HNSCC) present with locally advanced disease (1). In this patient group, multidisciplinary therapy is generally recommended with either surgery followed by adjuvant radiotherapy (RT) or radiochemotherapy (aRCT) or definitive RCT (1). Patients with locally advanced head and neck squamous cell carcinoma often experience relapse, the cause of relatively worse survival. Microscopically involved resection margins (R1) and extracapsular spread (ECS) of lymph node metastases are the most significant prognostic factors (“high risk”) for poor outcome. Close margins (R0 <5 mm) and the presence of ≥ 2 lymph node metastases represent “intermediate-risk” features predictive for worse disease control (2, 3). Unfortunately, and despite advantages in imaging diagnostics and therapy regimens in the curative setting, even completely resected high and intermediate risk HNSCC are prone to loco-regional recurrence and/or distant metastasis and about 45 to 50% of patients experience such an event or even death within 24 months (1–4). The surgical concepts for advanced resectable HNSCC have not changed significantly within the last 20 years. In experienced centers, additional techniques like transoral laser or robotic microsurgery (TLM, TORS) to conventional surgical approaches and neck dissection are standard procedures for treatment of advanced resectable HNSCC. The addition of concomitant cisplatin to aRT as aRCT improves outcome in patients with intermediate and high risk who are fit to receive chemotherapy (4). The HPV-related prognostic impact in oropharyngeal cancer did not change the standard treatment until yet and is currently under investigation in clinical trials. Despite the currently available treatment options for patients with locally advanced HNSCC, there is a need for better therapies in the curative setting for this patient population. Strategies to improve survival with intensified therapy for patients with high-risk HNSCC have been limited by excessive toxicity (5).

Since the first publication of the beneficial use of checkpoint inhibitors in HNSCC, these have been explored in different clinical settings. Pembrolizumab is a potent and highly selective humanized, monoclonal anti–programmed death receptor-1 (PD-1) antibody that has demonstrated robust antitumor activity and an acceptable safety profile in different cancer entities (6). Pembrolizumab is approved for recurrent/metastatic HNSCC with disease progression on or after platinum-containing chemotherapy and previously untreated recurrent/metastatic HNSCC. The approval is based on the positive results of the KEYNOTE-040 trial, evaluating pembrolizumab monotherapy in patients whose HNSCC progressed after platinum therapy (7), and the KEYNOTE-048 trial, evaluating pembrolizumab, alone or in combination with chemotherapy, in patients who did not previously receive systemic therapy for recurrent/metastatic disease (8). Although pembrolizumab is approved for recurrent/metastatic disease, its role in the primary management of locally advanced HNSCC is not defined. The relevant prolongation of overall survival (OS) and favorable safety profile of pembrolizumab in patients with recurrent or metastatic HNSCC (7, 8) support the further evaluation of pembrolizumab in earlier stages of disease. The ADRISK trial wants to investigate if the addition of pembrolizumab to aRCT with cisplatin improves event-free survival (EFS) compared with aRCT alone in locally advanced intermediate- and high-risk HNSCC.

## Methods

### Study design

ADRISK is a prospective, randomized, open-label, two-armed phase II multicenter superiority trial within the German Interdisciplinary Study Group of German Cancer Society (IAG-KHT). Patients with primary resectable stage III and IV (according to 7^th^ edition of TNM classification) HNSCC of the oral cavity, oropharynx, hypopharynx and larynx with pathologic high (R1, extracapsular nodal extension) or intermediate risk (R0 <5 mm; N≥2) after surgery who are eligible for cisplatin-based aRCT after surgery will receive either standard aRCT with cisplatin versus the same treatment + pembrolizumab (200 mg iv, in 3-week cycle, max. 12 months) (**Figure 1**). This clinical trial has been approved by the ethics committee of the University of Leipzig (076/18-ff).

**Figure 1 f1:**
[figure not shown]
Study design of the ADRISK trial.

All persons participating in the conduct of the trial (sponsor, authorized representative of the sponsor, investigators, etc.) commit themselves to observe the Declaration of Helsinki of the WMA in its current version, as well as all pertinent national laws and the ICH guideline for Good Clinical Practice (GCP) ICH E6(R2) (EMA/CHMP/ICH/135/1995) issued in June 2017. The trial is registered on the clinicaltrials.gov database (NCT03480672).

### Study objectives

The primary objective of ADRISK is to show that addition of pembrolizumab to aRCT with cisplatin improves EFS compared with aRCT alone in locally advanced intermediate and high-risk HNSCC after surgery. The primary endpoint EFS is defined as time from randomization to the first event, i.e.:

locoregional or distant recurrence (relapse),occurrence of further malignant disease (independent from localization and type),death from any cause, andinitiation of a new anti-cancer treatment without a previous event (primarily in case of safety concerns/toxicities observed which must be addressed in the patient**’**s treatment).

Secondary goals of the trial are to show that addition of pembrolizumab to aRCT with cisplatin improves OS compared with aRCT alone in locally advanced intermediate and high-risk HNSCC and to assess toxicity and show that addition of pembrolizumab to aRCT with cisplatin is safe in terms of toxicity (early *and* late toxicity). The duration of patients**’** observation is planned for at least 24 months post randomization, but preferably until LPLV (last patient**’**s last visit after 24 months of observation) to collect endpoint-events as comprehensive as possible.

Within the trial PD-L1 and p16 (only at tumor site oropharynx) expression in tumor tissue will be characterized by immunohistochemistry to explore the relationship between tumor PD-L1 and p16 expression and response to treatment with pembrolizumab. Therefore, material collected during the tumor resection will be analyzed locally at trial site and validated by reference pathologists in the central lab.

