### Trial population

A sample of 240 patients was planned to be randomized at a 1:1 ratio (about half of the patients to each treatment arm) after stratification for q1w/q3w aRCT regimen and localization of tumor as well as p16-status in oropharynx cancer.

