#### Planned methods for analysis

Confirmatory analysis follows the intention to treat principle and will be based on the full analysis set. Time to event endpoints will be analyzed by Cox regression with arm as fixed effects, stratification criteria as fixed and center as random effect. The occurrence of safety endpoints (AE by Preferred Term/occurrences of toxicities of grades ≥3) will be compared by chi-square tests. Odds ratios with 95% confidence intervals will be provided. Serious adverse events will be reported descriptively (including a clinical causality assessment) by System Organ Class and Preferred Term according to MedDRA. In case of relevant frequencies of SAE and classified serious adverse reactions (by Preferred Term) exact Fisher test will be applied on SAE/SAR occurrences. No confirmatory subgroup analyses are planned. PD-L1 status will be analyzed in exploratory analyses. Safety issues will be carefully monitored. Regular safety analyses will be performed and presented to the Data-Monitoring Committee (DMC). Statistical monitoring will focus on data quality assurance. All analyses will be pre-specified in a detailed statistical analysis plan, which will be finalized before data base closure. The trial will be reported according to CONSORT criteria.

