## Conclusion

ADRISK is a randomized, phase II trial aiming to investigate if the addition of pembrolizumab to aRCT with cisplatin improves EFS and OS and is safe in terms of toxicity compared with aRCT alone in locally advanced intermediate and high-risk HNSCC. The ADRISK trial started recruitment in August 2018 and plans to include 240 patients.

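### The secondary goal of showing that adding pembrolizumab is safe claims more than the planned difference tests on toxicity can support

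*Protocol article*

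**What the plan says.** Study objectives gives the secondary goals as showing an improvement in overall survival, and assessing toxicity together with a demonstrative aim: to "show that addition of pembrolizumab to aRCT with cisplatin is safe in terms of toxicity", covering early and late toxicity.

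Planned methods for analysis then fixes how toxicity is compared:

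- "The occurrence of safety endpoints (AE by Preferred Term/occurrences of toxicities of grades ≥3) will be compared by chi-square tests".
- Each comparison is to carry an odds ratio and its 95% interval.
- Serious adverse events are described by System Organ Class and Preferred Term with a causality assessment. Where frequencies are relevant, an "exact Fisher test will be applied on SAE/SAR occurrences".
- "Regular safety analyses will be performed and presented to the Data-Monitoring Committee (DMC").

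Study design calls this a "prospective, randomized, open-label, two-armed phase II multicenter superiority trial". Estimation of sample size rests on event-free survival alone. Trial population plans 240 patients at 1:1, so about 120 per arm. Table 4, footnote 4, collects adverse events in the experimental arm until 90 days after treatment ends or a new anti-cancer treatment starts, but in the control arm only to the first efficacy follow-up at month 3.

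**The concern.** The chi-square and Fisher tests take equal rates in the two groups as their null hypothesis. A small p-value is evidence of a difference. A large one means only that no difference was established, and with 120 per arm that leaves room for a relevant excess. The objective asks for the opposite kind of evidence, a positive demonstration of safety, and neither test can supply it. The planned odds-ratio intervals are the right kind of evidence, but the article does not connect them to the objective.

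This matters because toxicity will weigh on whether the combination is taken further. The Introduction itself notes that earlier attempts to intensify treatment in high-risk disease were held back by excessive toxicity. A statement that safety has been shown should not rest on an analysis that could miss a 10-point rise in severe toxicity more often than it finds it.

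**Working it through.** **The plan's own power figure.** The only one concerns event-free survival: 93 events for a hazard ratio of 0.6, one-sided 5%, 80% power. Schoenfeld's formula is 4(1.645 + 0.842)² / (ln HR)².

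- HR 0.6 gives 95.
- The ratio implied by 55% to 70%, ln 0.70 / ln 0.55 = 0.597, gives 93.

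So the figure reproduces and is not in dispute. No corresponding figure is given for safety.

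**Inputs for the safety check.**

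- n = 120 per arm, from 240 at 1:1. This is approximate, because Analysis population groups safety patients by whether they received any pembrolizumab.
- Two-sided 5% level: assumed.
- Control toxicity rate p₀: assumed, shown as a range.
- True excess d: 10 or 15 percentage points, assumed.

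**Power of the difference test.** With p₁ = p₀ + d and p̄ = (p₀ + p₁)/2:

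Power = Φ{(d − 1.96·SE₀)/SE₁}, where SE₀ = √[2p̄(1−p̄)/120] and SE₁ = √[(p₀(1−p₀) + p₁(1−p₁))/120].

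For p₀ = 0.50 and d = 0.10: SE₀ = 0.0642, SE₁ = 0.0639, so Φ{(0.10 − 0.1259)/0.0639} = Φ(−0.405) = 0.34.

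| Control rate | Power, +10 points | Non-significant, +10 points | Power, +15 points |
|---|---|---|---|
| 10% | 0.58 | 42% | 0.87 |
| 20% | 0.43 | 57% | 0.74 |
| 40% | 0.34 | 66% | 0.64 |
| 50% | 0.34 | 66% | 0.65 |
| 60% | 0.37 | 63% | 0.70 |
| 70% | 0.43 | 57% | 0.80 |

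**Precision.** The 95% interval half-width for the risk difference is 1.96·SE₁. Over control rates of 40-60% and excesses of 10-15 points it is 0.117 to 0.125, about 12 points.

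**Illustration.** With 72/120 (60%) against 84/120 (70%), the chi-square without continuity correction is 2.64, p = 0.10. The odds ratio is (84 × 48)/(36 × 72) = 1.56, 95% CI 0.91 to 2.66. The risk difference is 10 points, with 1.96 × 0.0612 = 12 points either side, so −2 to +22. The result is non-significant, yet compatible with an excess of 20 points.

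**What a demonstration would need.** For a margin m, equal true rates p, one-sided 2.5% and 80% power, n per arm = 2p(1−p)(1.96 + 0.842)²/m². At p = 0.50 this gives 393 for a 10-point margin, 175 for 15 points and 99 for 20 points. At common toxicity rates, 120 per arm could therefore support a claim only against a margin near 20 points. These margins illustrate scale; none is proposed.

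**The case against.** The case for leaving the text alone has real substance.

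- *The goal also says to assess toxicity.* True, and that half is an estimation aim that the plan can meet. The demonstrative half remains beside it.
- *Confidence intervals, descriptive reporting of serious events and committee reviews are already planned.* True; safety is not judged by chi-square alone. But no stated conclusion depends on the intervals, and committee monitoring serves the conduct of the trial rather than the final claim.
- *A criterion for safety may sit in the full protocol or analysis plan.* It may, and a missing threshold alone would be no finding in an article. The point rests on two things that are both stated here, the objective and the tests. A detail elsewhere would not make a difference test demonstrate safety.
- *The Conclusion repeats the claim.* A reader might infer this from the words "is safe in terms of toxicity compared with aRCT alone", but that sentence is framed as a question under investigation, so it is not demonstrative.

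Two stronger readings are tempting. The first is that the plan treats p > 0.05 as proof of safety. The article contains no such rule; this is a misreading that the wording allows. The second is that any relevant rise in toxicity would probably be non-significant. That fails for a 15-point excess, where power is 64-70% at control rates of 40-60%, and for a 10-point excess at a 10% control rate, where power is 58%. The longer adverse-event window in the experimental arm and the many Preferred Term tests also push towards finding some difference.

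**Conclusion.** The mismatch stands: one half of a secondary objective asks for a demonstration of safety, and the stated tests can only look for a difference. At control grade ≥3 rates of 40-60%, a true 10-point excess would go undetected in roughly two trials in three, and in 42% of trials at a 10% control rate. These figures assume about 120 per arm, a two-sided 5% level and equal observation of both arms; the toxicity rates are assumptions because the article gives none. The point concerns what the trial may conclude about a secondary objective. It does not touch the primary analysis or its sample size. It should be corrected, since the correction is nearly free.

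**What to change.** 1. In Study objectives, replace the aim of showing safety with assessing and estimating the difference in toxicity between the arms. The Conclusion needs no change.
2. Base the safety conclusion on the risk difference, experimental minus control, in the proportion of patients with any grade ≥3 toxicity, with its 95% confidence interval, over the window in which adverse events are collected in both arms. Under Table 4, footnote 4, that window ends at month 3. Report later toxicity in the experimental arm descriptively.
3. State that a non-significant chi-square or Fisher test will not be reported as showing safety.
4. If the sponsor wants a safety claim, judge it by the upper confidence limit of that difference against a limit that the sponsor fixes before database closure.

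This changes only the wording of the objective and the analysis plan; no further patients are needed. The costs are a more modest safety claim and a comparison that covers about 13 of the 51 weeks of pembrolizumab. The comparative measure would not address the late toxicity named in the objective unless the collection windows were aligned, which would mean collecting more control-arm data.

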### Trial population

A sample of 240 patients was planned to be randomized at a 1:1 ratio (about half of the patients to each treatment arm) after stratification for q1w/q3w aRCT regimen and localization of tumor as well as p16-status in oropharynx cancer.

#### Inclusion criteria

1. Macroscopically complete resection of newly diagnosed (not recurrent, not secondary primary) advanced squamous-cell carcinoma arising in the oral cavity, oropharynx, larynx, or hypopharynx2. Advanced stage III, IVA/B HNSCC according to the TNM classification version 7th edition3. Eastern Cooperative Oncology Group (ECOG) performance status of 0 to 1; performance status allows adjuvant chemo radiation with cisplatin.4. Had either intermediate or high-risk characteristics, i.e. any or all of the following: - histologic evidence of invasion of two or more regional lymph nodes - extracapsular extension of nodal disease, - microscopically involved mucosal margins of resection (R1) or margins of resection < 5mm (R0)5. Had pathological histologic assessment of p16 (only oropharyngeal carcinoma)6. Be > 18 years of age7. Written informed consent8. Demonstrate adequate organ function as defined in **Table 1**; all baseline labs should be performed within 10 days of treatment initiation.9. Female subject of childbearing potential should have a negative pregnancy test within 3 days prior to receiving the first dose of study medication.10. Female subjects of childbearing potential must be willing to use an adequate method of contraception, for the course of the study through 120 days after the last dose of study medication.11. Reproductive male subjects must agree to use an adequate method of contraception, starting with the first dose of study therapy through 120 days after the last dose of study therapy.

**Table 1 T1:** Adequate organ function laboratory values.

System	Laboratory value
**Hematological** Absolute neutrophil count (ANC) Platelets Hemoglobin	≥1,500/μL 1≥ 100,000 μL ≥9 g/dL or ≥5.6 mmol/L without transfusion or EPO dependency (Criteria must be met within last 2 weeks)
**Renal** Serum creatinine **OR** Measured or calculated creatinine clearance (GFR can also be used in place of creatinine or CrCl)	≤1.5x upper limit of normal (ULN) **OR** ≥60 mL/min for subject with creatinine levels > 1.5 X institutional ULN
**Hepatic** Serum total bilirubin AST (SGOT) and ALT (SGPT) Albumin	≤ 1.5x ULN **OR** Direct bilirubin ≤ ULN for subjects with total bilirubin levels > 1.5 ULN ≤ 2.5x ULN **OR** **≤** 5x ULN for subjects with liver metastases >2.5 mg/dL
**Coagulation** International Normalized Ratio (INR) Activated Partial Thromboplastin Time (aPTT)	≤1.5x ULN unless subject is receiving anticoagulant therapy as long as aPTT is within therapeutic range of intended use of anticoagulants

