#### Chemotherapy

The q1w and q3w schedule will be allowed in the ADRISK and may be applied according to the respective standard of the center. The dosing and timing of chemotherapy to be used in this trial is outlined in **Table 2**. These options were chosen since the q3w schedule is not very common in Germany. However, the balancing of the cisplatin/RT doses will be reviewed permanently to rule out bias between the arms and the cisplatin schedule is used as a stratification criterion. A minimum of 200 mg/m^2^ cisplatin should be aimed at in all patients. An intravenous infusion (volume replacement) will be given as supportive therapy. All patients receive adequate antiemetic prophylaxis. The choice between q1w and q3w is left to the appraisal of the radiation oncologist, considering age, weight loss before radiation, creatinine clearance and performance status. In practice, various radiotherapists systematically use q1w cisplatin, and others use q3w cisplatin. In case of poor radiochemotherapy tolerability, the patients have to be hospitalized or receive a nasogastric intubation.

**Table 2 T2:** Cisplatin treatment.

Drug	Dose/Body Surface Area	Frequency Dose/Body Surface Area	Route of Administration	Regimen/Treatment Period
Cisplatin	300 mg/m^2^	q3w 100 mg/m^2^	inravenous infusion	days 1, 22, and 43
Cisplatin	280 mg/m^2^	q1w 40 mg/m^2^	intravenous infusion	days 1, 8, 15, 22, 29, 36, 43 1-7th week

Patients must meet the following criteria before each new cycle:

• No hematotoxicity of grade ≥2 (i.e. neutrophils >1500/μL, platelets >100.000/μL, hemoglobin ≥9 g/dl, if required after transfusion)• Recovery from any treatment-related grade 3/4 non-hematological toxicity (except alopecia) to baseline or ≤grade 1• No ongoing requirement for anti-diarrheic treatment• Bilirubin ≤3.0 x ULN• Transaminases ≤2.5 x ULN• No peripheral neurotoxicity of grade 3• Creatinine clearance ≥60 mL/min• No treatment delay of more than 3 weeks

Patients not meeting the above criteria on the date scheduled for the new cycle must suspend treatment with the anticancer drugs until they meet the above criteria. In the case of a cisplatin intolerance during RCT, it may be possible to switch to carboplatin. The administration of mitomycin is not permitted.

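### The renal entry limit is looser than the renal dosing limit, so a patient can qualify for the trial and then fail the rule for receiving cisplatin

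*Protocol article*

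**What the plan says.** **Entry (Inclusion criteria, criterion 8 and Table 1, Renal).** There are two alternative routes. Serum creatinine of at most 1.5 times ULN is sufficient alone. Otherwise, measured or calculated clearance must be "≥60 mL/min for subject with creatinine levels > 1.5 X institutional ULN". GFR may replace either measure, but this is optional.

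**Dosing (Chemotherapy, criteria before each new cycle).** The list includes "Creatinine clearance ≥60 mL/min", with no creatinine alternative. Patients who fail any item "must suspend treatment with the anticancer drugs until they meet the above criteria". The same list allows no treatment delay of more than 3 weeks.

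**Related text.**
- Study design describes the population as "eligible for cisplatin-based aRCT after surgery".
- The Chemotherapy section leaves the choice of weekly or three-weekly cisplatin to the radiation oncologist, "considering age, weight loss before radiation, creatinine clearance and performance status".
- It also sets a dose target: "A minimum of 200 mg/m^2^ cisplatin should be aimed at in all patients".

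**The concern.** An entry criterion should admit only patients who can start and continue the protocol treatment. Here the patients allowed a dose are a strict subset of those allowed to enter, and the difference lies in renal function, one of the factors the protocol itself weighs when choosing the cisplatin schedule.

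A site with a patient in the gap has two options. It can withhold cisplatin from someone admitted to receive it, which works against the dose target. Or it can give cisplatin below the protocol's own clearance floor.

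The stake is treatment delivery and patient safety. The rule is applied before randomization and is the same in both arms. It does not by itself remove patients from the full analysis set, change the EFS events, bias the comparison or reduce power.

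**Working it through.** The plan gives no figure to reproduce on this point. The check has three parts: compare the rules, see whether the gap can be reached by plausible patients, and see what suspension does to the dose target.

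**1. The rules side by side**

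| Item | Entry (Table 1) | Before each new cycle (Chemotherapy) |
|---|---|---|
| Renal | creatinine ≤1.5×ULN, or clearance ≥60 mL/min if creatinine is above that | clearance ≥60 mL/min |
| Bilirubin, main limit | ≤1.5×ULN | "Bilirubin ≤3.0 x ULN" |
| Transaminases, main limit | ≤2.5×ULN | ≤2.5×ULN |
| Haemoglobin | ≥9 g/dL | ≥9 g/dL |

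On the main limits, only the renal row is looser at entry than at dosing. The gap is creatinine ≤1.5×ULN with clearance <60 mL/min.

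**2. Can the gap be reached?**

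Assumptions, none of them from the documents: Cockcroft-Gault formula for men; age 50, 60 or 70 years; weight 60, 70, 80 or 90 kg (12 profiles); ULN 1.1, 1.2 or 1.3 mg/dL.

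Clearance = (140 − age) × weight / (72 × creatinine).

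Setting clearance to 60 gives a threshold creatinine of (140 − age) × weight / 4320:

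| Age | 60 kg | 70 kg | 80 kg | 90 kg |
|---|---|---|---|---|
| 50 | 1.25 | 1.46 | 1.67 | 1.88 |
| 60 | 1.11 | 1.30 | 1.48 | 1.67 |
| 70 | 0.97 | 1.13 | 1.30 | 1.46 |

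(mg/dL)

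- As a multiple of ULN, the threshold runs from 0.97/1.3 = 0.75 to 1.88/1.1 = 1.70.
- The entry limit of 1.5×ULN is 1.65, 1.80 or 1.95 mg/dL. The threshold lies below it in 9, 11 and 12 of the 12 profiles respectively. In each of these, some range of creatinine passes entry and fails the cycle rule.
- Clearance at exactly 1.5×ULN runs from 70 × 60 / (72 × 1.95) = 29.9 to 90 × 90 / (72 × 1.65) = 68.2 mL/min.
- Example: 60 years, 70 kg, ULN 1.2 mg/dL. Clearance is 5600 / (72 × creatinine), which gives 64.8, 51.9 and 43.2 mL/min at 1.2, 1.5 and 1.8 mg/dL. All three values pass Table 1; the last two fail the cycle rule.

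A second grid (same ages and ULN; 55, 70 and 85 kg) gives clearance below 60 mL/min at 1.5×ULN in 26 of 27 combinations.

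**3. What suspension does to the dose target**

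The target of 200 mg/m² needs 200/100 = 2 of the 3 planned three-weekly doses, or 200/40 = 5 of the 7 weekly doses. That leaves room to miss one or two doses. A patient whose low clearance is stable will not recover it by waiting, delay is capped at 3 weeks, and radiochemotherapy lasts at most seven weeks (Plan for further treatment). Suspension can then become loss of cisplatin.

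**The case against.** The strongest reply is that other text closes much of the gap in practice. The population must be fit for cisplatin-based treatment. Cisplatin schedule is a stratification factor, so it is chosen before randomization with clearance in view. A site would have to see a low clearance, still judge the patient fit for cisplatin, and randomize. This does lower the likely frequency. But neither passage gives a cutoff, inclusion criterion 3 speaks only of performance status, and the criterion that defines renal adequacy is Table 1.

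Other points on that side:

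- **Dosing below 60 mL/min would be a protocol violation, since the stricter rule governs.** This is correct if the rule covers cycle 1. The wording leaves that open; if cycle 1 is not covered, the first dose can be given below the floor without a violation.
- **Suspension is conditional, carboplatin is allowed, and 200 mg/m² is only an aim.** All true. The switch is for cisplatin intolerance arising during radiochemotherapy, though, and does not lift the suspension rule.
- **Frequency is unknown.** This stands. The profile counts show that the gap exists, not how many patients fall in it. With creatinine exactly at ULN, clearance is below 60 mL/min in only 1, 3 and 6 of the 12 profiles (ULN 1.1, 1.2, 1.3 mg/dL); the other profiles reach the gap only with raised creatinine.
- **Bilirubin has a similar side route.** Table 1 sets no upper limit on total bilirubin when direct bilirubin is within ULN, while the cycle rule caps it at 3.0×ULN. This also stands, which is why the comparison above is confined to main limits. It does not answer the renal conflict.

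**Conclusion.** The concern holds. Two printed numerical rules conflict for patients with creatinine within 1.5×ULN and clearance below 60 mL/min. That conclusion needs no outside assumption. That ordinary patient profiles can fall in the gap rests on the Cockcroft-Gault formula and the assumed ages, weights and ULN values. The proportion of the planned 240 patients affected cannot be derived from the documents.

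The consequence is limited to cisplatin delivery and safety. It should be corrected, but it does not threaten the comparison of the arms.

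**What to change.** - In Table 1, require measured or calculated creatinine clearance, or GFR, of at least 60 mL/min at entry for all patients, and drop the route by creatinine alone. The entry and dosing rules then coincide and the gap is empty.
- In the Chemotherapy section, state whether the criteria before each new cycle apply to cycle 1.
- Apply the change to patients not yet randomized; the article describes recruitment as ongoing.
- While amending Table 1, check the albumin limit. As printed (above 2.5 mg/dL) it excludes no one. It was presumably meant as 2.5 g/dL, which the sponsor should confirm. This is a separate, minor point.

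The cost is a small eligibility amendment, one clarifying sentence and possibly a few fewer eligible patients. Sample size, endpoint and analysis do not change.
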